## Abstract

**Background:**

A proportion of patients undergoing midline laparotomy will develop surgical site infections after surgery. These complications place considerable financial burden on healthcare economies and have negative implications for patient health and quality of life. The prophylactic application of negative pressure wound therapy devices has been mooted as a pragmatic strategy to reduce surgical site infections. Nevertheless, further availability of multicentre randomized clinical trial data evaluating the prophylactic use of negative pressure wound therapy following midline laparotomy is warranted to definitely provide consensus in relation to these closure methods, while also deciphering potential differences among subgroups. The aim of this study is to determine whether prophylactic negative pressure wound therapy reduces postoperative wound complications in patients undergoing midline laparotomy.

**Methods:**

PROPEL-2 is a multicentre prospective randomized clinical trial designed to compare standard surgical dressings (control arm) with negative pressure wound therapy dressings (Prevena™ and PICO™ being the most commonly utilized). Patient recruitment will include adult patients aged 18 years or over, who are indicated to undergo emergency or elective laparotomy. To achieve 90% power at the 5% significance level, 1006 patients will be required in each arm, which when allowing for losses to follow-up, 10% will be added to each arm, leaving the total projected sample size to be 2013 patients, who will be recruited across a 36-month enrolment period.

**Conclusion:**

The PROPEL-2 trial will be the largest independent multicentre randomized clinical trial designed to assess the role of prophylactic negative pressure wound therapy in patients indicated to undergo midline laparotomy. The comparison of standard treatment to two commercially available negative pressure wound therapy devices will help provide consensus on the routine management of laparotomy wounds. Enrolment to PROPEL-2 began in June 2023.

**Registration number:** NCT05977816 (http://www.clinicaltrials.gov).

## Introduction

In recent decades, contemporary surgical practice has focused upon optimizing perioperative factors to enhance clinical outcomes for patients indicated to undergo surgery^1^. Surgical site complications remain a significant burden on surgical practice^2^, having negative implications on patient health, quality of life metrics and the cost effectiveness of the provision of surgical care. Surgical site infections (SSIs) are defined as incision or deep tissue infections at the operation site occurring up to 30 days after surgery^3^. SSIs constitute negative implications for surgical patients' postoperative recovery, through prolonging inpatient hospital stays, necessitating additional antimicrobial treatment, and in severe cases, leading to reintervention^4,5^.

Recent efforts have focused on identifying novel strategies to reduce SSIs^6,7^, yet the average incidence remains consistent in 0.5–3.0% of all surgical patients^8^ and 11.0% of general surgery patients^9^. Randomized clinical trial (RCT) data illustrates that SSIs have an incidence of 15–25% following colorectal and emergency abdominal surgery^10–12^.

The hypothesis supporting the use of suction-based drainage of infected wounds was first described by Soviet scientists in the mid-1980s for complex, contaminated wounds, with these preliminary results supporting their use in such cases^13,14^. The prophylactic application of negative pressure wound therapy (NPWT) devices was subsequently proposed as a novel strategy to combat chronic wound infections, following the publication of promising results from an animal study in 1997^15^. Thereafter, the application of NPWT for wound complications came into vogue^16,17^: in 2016, Hyldig *et al*. performed a meta-analysis of 10 RCTs which illustrated a relative risk reduction of 50% for wound infection and seroma formation relative to standard dressings^18^, albeit results were limited due to heterogeneity between the studies included. Sahebally *et al*. then performed a meta-analysis of 1266 patients which demonstrated a 75% relative reduction in SSI for patients who had NPWT applied to their closed abdominal surgery wounds^19^.

PICO™ (Smith & Nephew, London, UK) and Prevena™ (KCI, 3M, St Paul, MN, USA) wound management systems are among the most widely used NPWT in surgical practice. Importantly, the PICO trial performed in 2017 illustrated a significant reduction in SSI rate and duration of hospital stay when compared with standard wound dressings^20^. Conversely, the NEPTUNE trial failed to identify any difference in wound infection rates postlaparotomy when comparing Prevena™ to standard dressings in patients undergoing colorectal surgery^21^. Data from the CHIR-Net, PROUD and ROSSINI RCTs demonstrated an incidence rate of 15–25% following gastrointestinal surgery^10–12^, with significant morbidity rates and costs^22^. Furthermore, most trials included short durations of follow-up (median: 7 days)^23^, with no trials comparing different types of NPWT and conflicting results from different devices trialled^21,22^. Additionally, there are limited data available on economic analyses for gastrointestinal surgery indications^23^. Accordingly, the necessity to identify novel interventions to reduce SSI incidence is imperative, yet given the heterogeneity of results, there are no consensus statements or guidelines recommending the routine use of prophylactic NPWT to prevent SSI postlaparotomy.

Thus, the aim of the PROPEL-2 trial is to determine whether NPWT confers a lower rate of SSI following laparotomy. The hypothesis is that patients randomized to NPWT will have a lower incidence of SSI.

## Methods

### Trial design

PROPEL-2 is a prospective, multicentre RCT recruiting patients from surgical units across the Republic of Ireland designed in accordance with the CONSORT guidelines for prospective, two parallel group randomized studies^24^. This trial was prospectively registered at http://www.clinicaltrials.gov as NCT05977816.

Patients recruited to this study may be randomized to Standard dressing or NPWT (that is: PICO™, Prevena™, etc.). The control arm will be randomized to receive a standard transparent waterproof dressing.

PROPEL-2 will have two phases. Phase I (internal pilot) is designed to confirm the expected recruitment rate for a large-scale multicentre RCT. Phase 2 (main phase) will be the proposed RCT in centres across the island of Ireland.

#### Internal pilot summary

The pilot will be conducted over an interval of 6 months, including secondary and tertiary referral centres. The internal pilot aims to determine the number of eligible and recruited patients in the centres over the course of 6 months. If recruitment targets are not achieved a review of the reasons will be investigated in terms of ineligibility due to protocol eligibility requirements, poor site performance and lack of suitable patient population. If targets are met, and any issues resolved, the trial will proceed into the main phase, including patients from the internal pilot. If the trial does not progress to Phase 2, those participants already enrolled in Phase 1 will be followed up as per protocol.

All adult patients presenting at trial centres requiring surgery via a midline laparotomy incision as the primary operative access are eligible for inclusion. Patients will be excluded if pregnant, if they have undergone a relook laparotomy, if their abdomen is left open or if unable to adhere. Randomization will be stratified by trial centre, emergency or elective procedure, and surgical specialty (upper gastrointestinal, lower gastrointestinal, general, vascular, urology). Randomization will be generated and administered via a secure web service, Sealed Envelope, using minimization. The random allocation will be to either standard wound dressing or single-use NPWT. Participating patients will have clinical follow-up for 6 months. Wound photographs will be taken at 1-month, 3-month and 6-month visits. The photograph at 1 month will assist with diagnosis of any infection. Photographs from the 1-month, 3-month and 6-month visits will be used by the clinician to evaluate wound healing together with a patient-reported assessment using the patient and observer scar assessment scale (POSAS) questionnaire^25^. EuroQol 5-Dimension 5-level (EQ5D-5L) quality of life questionnaires will be completed before surgery and at 1 month, 3 months and 6 months to collect quality of life outcome data^26^. At 3 and 6 months, the patient will complete a Cost for Patients Questionnaire (CoPaQ) to evaluate the financial impact on the patient^27^. Information regarding resource use, late complications or additional interventions related to their index procedure will be used to evaluate the financial impact on the healthcare system. Patient monitoring will be performed by the clinical teams responsible for the management of these patients after surgery.

### Treatment arms

#### Standard dressing

The standard dressing for a laparotomy wound comprises a non-adhesive layer applied directly to the wound covered by a sealed dressing and does not use negative pressure.

The materials used will be at the discretion of the surgeon but details of each NPWT dressing applied will be noted. Acceptable standard dressings include Mepore© (Molnlycke Healtcare, Gothenberg, Sweden), Opsite© (Smith and Nephew, London, UK) and Tegadrem© (3M, MN, USA), among others.

### Negative pressure wound therapy

NPWT dressings use an open cell foam laid on top of the wound. It is then covered with an impermeable adhesive membrane. A sealed tube punctures the membrane to connect the dressing to the in-built pump leading to the creation of a partial vacuum of the wound. Generally, the first dressing applied at the end of the operation is left in place until the wound is ready for sutures to be removed at approximately 7–10 days. The number of replacement NPWT dressings within the first 30 and 90 days will be captured.

The Prevena^TM^ (Kinetic Concepts Inc, San Antonio, TX, USA) Incision Management system is comprised of a suction unit that has a small canister for fluid collection, tubing and a sponge dressing with a non-adherent layer and semipermeable adhesive drape. Prevena^TM^ contains a 0.019% ionic silver solution which has utility in preventing bacterial growth in the dressing. The system is ergonomic as it is supplied with a carrying case to minimize negative implications on patient mobility. When applied and activated, this system maintains a closed environment and removes any potential fluid which may collect at the wound site via the application of negative pressure therapy.

The PICO^TM^ (Nephew Wound Management, London, UK) is a NPWT system that consists of a silicone wound interface dressing that is applied directly onto the wound. The purpose of this interface is to transmit even pressure distribution across the wound bed, while negative pressure is transmitted from the wound filler at −80 mmHg.

### Study objectives

The primary objective for the trial is to quantify and analyse differences in the rates of midline wound SSI in the 30 and 90 days following laparotomy between NPWT and standard dressings. The diagnosis of SSI will be made using Centre for Disease Control criteria.

The secondary objectives are to analyse health-related quality of life in the 6 months following laparotomy and to assess the quality of wound healing and cost effectiveness. Another objective is to analyse the further interventions related to laparotomy and the risk of developing SSI related to the subcutaneous adiposity and lean muscle mass using preoperative computed tomography (CT). In a nested Study Within A Trial (SWAT), another objective is to determine the impact of digital prompts (for example using e-mail) to research team members on site trial recruitment rates.

### Outcome measures

#### Primary outcome measure

The primary outcome measure is the incidence of any SSI. The treating clinical team who will make the diagnosis will not be members of the research team. For the purposes of the trial, any wound infection requiring ongoing medical intervention/which has led to reoperation at or after the 30 and 90 day review will be considered a deep SSI.

#### Secondary outcome measures

The secondary outcome measures in this trial are to compare the use of standard dressings with NPWT dressings in terms of impact on quality of life (QoL), with the EuroQoL EQ-5D-5L questionnaire and Quality Adjusted Life Year (QALY) profiles^26^, wound healing and scar appearance (using the POSAS questionnaire and the photograph taken at each follow-up visit)^25^, postoperative complications (obtained from the patient chart for this study) and economic settings (using the validated CoPaQ questionnaire for patients^27^). Incidence rates of skin blistering, allergic reactions to dressings and device/dressing malfunction were also evaluated. *Figure 1* outlines the CONSORT diagram for the PROPEL-2 trial.

**Fig. 1. zrae081-F1:**
[figure not shown]
CONSORT diagram for the PROPEL-2 trial

A subanalysis evaluating the relationship between preoperative subcutaneous adiposity and lean muscle mass on postoperative SSI will be performed. Adiposity and muscle mass data will be collected using preoperative computed tomography images. A SWAT will assess the impact of digital prompts on trial recruitment rates.

### Power calculation

For planning purposes, it is assumed 15% of participants randomized to standard dressings will develop an SSI and the rate among patients receiving prophylactic, single-use NPWT will be 10% (that is a relative risk reduction of 33%, absolute risk reduction 5%). To achieve 90% power at the 5% significance level, a minimum of 1006 patients will be required in each arm. To allow for losses to follow-up and withdrawals, 10% will be added to each arm. Therefore, the total projected sample size for PROPEL-2 is 2013 patients. This power calculation for PROPEL-2 did not estimate or account for subgroups, including elective and emergency laparotomy wounds or surgical procedures performed.

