The primary focus will be to compare the two treatment groups on an intention-to-treat (ITT) basis, and this will be reflected in the analysis which will be reported together with appropriate diagnostic plots that check the underlying model assumptions. In addition to the ITT analyses, per-protocol (as treated) analyses will also be undertaken and reported in parallel to, but subsidiary to, the main analyses. Where possible the reasons for missing data will be determined. Although missing data is not expected to be a problem for this study, the nature and pattern of the ‘missingness’ will be considered—including in particular, whether data can be treated as missing at random (MAR). If judged appropriate, missing data will be imputed, using multiple imputation. The resulting imputed data sets will be analysed and reported, together with appropriate sensitivity analyses. Any imputation methods used for scores and other derived variables will be reviewed by the Data Monitoring Committee (DMC). Reasons for ineligibility, non-compliance, withdrawal or other protocol violations will be stated if available and any patterns summarized. More formal analysis, for example using logistic regression with ‘protocol violation’ as a response, may also be appropriate and aid interpretation.

All reported tests will be two-sided and considered to provide evidence for a significant difference if *P* values are less than 0.05 (5% significance level). A detailed statistical analysis plan (SAP) will be agreed with the DMC before commencement of the study. Any subsequent amendments to this initial SAP will be clearly stated and justified in the final report. Interim analyses of efficacy outcomes are not planned and will be performed only where requested by the DMC. Data will be analysed using Statistical Package for Social Sciences™ (SPSS™) version 26.0 (International Business Machines Corporation, Armonk, NY, USA).

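### The 1006 per arm given as the minimum for 90% power already contains the 10% loss allowance, so the stated total of 2013 does not follow from the text

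*Protocol article*

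**What the plan says.** The Power calculation section assumes that "it is assumed 15% of participants randomized to standard dressings will develop an SSI", against 10% with negative pressure therapy, an absolute difference of 5 percentage points. It continues that, for 90% power at the 5% level, "a minimum of 1006 patients will be required in each arm". The allowance for losses and withdrawals comes next: "10% will be added to each arm. Therefore, the total projected sample size for PROPEL-2 is 2013 patients".

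The Abstract (Methods) has the same sequence: "1006 patients will be required in each arm, which when allowing for losses to follow-up, 10% will be added to each arm", again ending at 2013 patients.

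Two further inputs stand elsewhere in the article. The Statistical analysis section states that "All reported tests will be two-sided", and the Randomization section specifies one-to-one allocation.

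**The concern.** The text presents three steps: a minimum of 1006 per arm, then 10% on top, then 2013 as the result. Twice 1006 is 2012, so the last step has added one patient instead of about 200. Either the minimum, the allowance or the total is misreported.

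This figure is the yardstick for the size of the trial. As worded, the trial needs 1006 evaluable patients per arm but enrols only enough to keep about 906 after the loss it expects. A trial run exactly to plan would then appear to fall 100 per arm short of its own requirement. Someone who noticed the mismatch and applied the wording literally could raise the target by 201 patients without need.

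**Working it through.** **Inputs (all from the protocol article)**

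- Infection rate with standard dressing 0.15, with negative pressure therapy 0.10, difference 0.05 (Power calculation)
- Power 90%, significance level 5% (Power calculation); two-sided (Statistical analysis)
- Allocation 1:1 (Randomization)
- Allowance for losses 10%, described as added to each arm (Power calculation, Abstract)

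**Step 1. The article's own sum**

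- 2 × 1006 = 2012. The stated total is 2013, so the difference is 1 patient.
- 1006 × 1.10 = 1106.6, rounded up to 1107 per arm; 2 × 1107 = 2214.
- 2214 − 2013 = 201 patients between the literal reading and the stated total.

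This contradiction does not depend on any sample-size formula.

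**Step 2. What the stated assumptions require**

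Unpooled variance:

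n = (z₀.₉₇₅ + z₀.₉₀)² × [p₁(1 − p₁) + p₂(1 − p₂)] / (p₁ − p₂)²

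= (1.95996 + 1.28155)² × (0.15 × 0.85 + 0.10 × 0.90) / 0.05²

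= (3.24151)² × 0.2175 / 0.0025 = 914.1, rounded up to 915 per arm.

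Pooled variance under the null hypothesis (mean rate 0.125):

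n = [1.95996 × √(2 × 0.125 × 0.875) + 1.28155 × √0.2175]² / 0.0025 = 917.3, rounded up to 918 per arm.

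Other variants, to see whether any yields 1006:

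| Method | Per arm |
|---|---|
| Pooled variance in both terms | 920 |
| Arcsine | 911 |
| Log odds ratio | 931 |
| Continuity-corrected | 957 |
| One-sided 5% | 748 (787 with continuity correction) |
| 80% power | 686 |
| 95% power | 1135 |

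None gives 1006.

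**Step 3. Where 1006 and 2013 come from**

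- 915 × 1.10 = 1006.5 per arm
- 2 × 1006.5 = 2013 in total, exactly

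The unpooled minimum with the 10% added therefore reproduces both the stated total and, apart from the half patient, the stated per-arm number. The pooled 918 would give 918 × 1.10 = 1009.8 per arm, which matches neither.

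**Step 4. Power at the relevant sizes**

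Power = Φ(√(n × 0.0025 / 0.2175) − 1.95996), unpooled:

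- n = 1006 evaluable per arm: √11.563 = 3.400; 3.400 − 1.960 = 1.440; power 92.5% (pooled 92.4%).
- 2013 enrolled with 10% lost: 1006.5 × 0.9 = 905.85, about 906 per arm; √10.41 = 3.227; 3.227 − 1.960 = 1.267; power 89.7% (pooled 89.6%).

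The small shortfall from 90% arises because the allowance was applied as a multiplication by 1.10. Dividing by 0.90 would give 915 / 0.9 = 1016.7, rounded up to 1017 per arm, or 2034 in total.

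**The case against.** The strongest reply is that this is a labelling slip with no effect on the trial. Both places give the same recruitment target, 2013. Power after the expected loss is within half a percentage point of 90%, and the design and analysis are untouched. That is right as regards power, and nothing here implies that the trial is materially too small. It does not rescue the statement, because the number named as the requirement is wrong and the total does not follow from it.

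A second reply is that the article nowhere says 1006 includes the allowance, so the cause is inferred. The direct contradiction is proved by the article's figures alone; the explanation rests on the exact match 2 × 915 × 1.10 = 2013, which needs one particular choice of formula and rounding. No other reading tried reproduces both numbers, but the sponsor holds the original calculation and can confirm it.

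A third is that 1006 might contain an unstated adjustment, for example for clustering by centre. The Power calculation mentions none, and the Statistical analysis section says clustering is not expected to be important. Even if such an adjustment existed, adding 10% to 1006 would still not give 2013.

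Finally, 1006.5 is not a number of patients and 2013 cannot be split equally. This is fair, and the corrected text should use whole numbers per arm.

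**Conclusion.** The concern holds. The article reports the loss-inflated figure of 1006 per arm as the minimum for 90% power and then claims to inflate it again. The requirement under its stated assumptions is 915 evaluable patients per arm (918 with pooled variance), 1830 in total. The gap between the wording and the stated total is 201 patients.

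The enrolment target of 2013 is consistent with the assumptions and can stand. With 10% lost, about 906 per arm remain, 9 fewer than 915, and power is about 89.7%. If 1006 per arm were in fact evaluable, power would be 92.5%.

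These results assume a two-sided 5% comparison of two proportions, 15% versus 10%, with equal arms and no design effect, as the article describes. The statement must be corrected because it is the article's only account of how the trial was sized, and it is wrong in both places where it appears.

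**What to change.** Check the original calculation, then restate it in the Abstract and in the Power calculation section along these lines: 915 evaluable patients per arm (1830 in total) give 90% power at a two-sided 5% level for 15% versus 10%, using the unpooled variance; adding 10% for losses and withdrawals gives a total of 2013, that is 1006 or 1007 per arm; if 10% are lost, about 906 per arm remain and power is about 89.7%.

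Keep the enrolment target at 2013. If exactly equal arms are wanted, 1007 per arm gives 2014. Only if the original calculation shows that 1006 evaluable per arm was truly intended would the total have to become 2214, and the reason for exceeding 915 would then need to be stated.

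The cost is two sentences in two places. No extra patients and no change to design or analysis are needed.

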### Ethical approval

The PROPEL-2 trial is designed in accordance with the principles of the Declaration of Helsinki and ‘good clinical practice’ guidelines^28^. The protocol has been approved by the ethics committee at Tallaght University Hospital/St. James Hospital, Dublin, and approval has been obtained from other participating centres. Written informed consent will be prospectively obtained before surgery. This study will receive no financial aid.

### Randomization

Eligibility will be confirmed by the treating surgeon at the end of the operative procedure before the wound dressing is applied. Randomization will be on a one-to-one basis using a computer randomization programme with the minimization algorithm to ensure a balanced allocation of patients across the two treatment groups, stratified by trial centre, emergency or elective procedure, and surgical specialty. The first 30 participants will be randomized using simple randomization in order to seed the minimization algorithm, which will have a probable cystic element incorporated to ensure unpredictability of treatment assignment.

